#### Participatory Action Research

Periodic reviews of process measures and feedback may result in iterative changes of the clinical model. The fidelity of clinic delivery to the original plan will be presented and analyzed.

#### Procedure for Dealing With Missing, Unused, and Spurious Data

Each outcome will be analyzed using measured data values of all patients. Patients with missing data will be excluded from the analyses. Suspicious data values will be checked against the source data. If there are outlying values, the analyses will be performed twice—once with the outlying values and once without the outlying values.

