### A New Model of Care

A high proportion of the costs for respiratory diseases is generated by a relatively small group of patients with severe disease (recognized or unrecognized) or complex problems that include multimorbidity, at-risk behaviors, and socioeconomic disadvantage. Such patients often struggle to engage with the structured, proactive care approach to chronic disease management advocated for asthma and COPD, resulting in repeated emergency health care use of both primary and secondary care. An integrated approach for the management of complex patients, incorporating both specialist and primary care teams’ expertise, may be effective in improving outcomes for such high-risk patients. However, the evidence is mixed, and there is a need for evaluations of models of integrated care in routine “real-world” clinical settings.

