#### Overall Description of Study Participants

Adult patients (aged ≥ 16 years) with poorly controlled asthma or COPD as well as those with undifferentiated breathlessness will be identified using GRASP tools; referred from a community pharmacist or by their primary care team; and invited to a local MISSION clinic with a relative, friend, or carer in attendance, if they wish. All eligible attendees will be invited to participate in the study. The sample size will be determined by the uptake of appointments and clinic capacity but is projected to be 500 patients and 15 HCPs.

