##### Disease Control, Disease-Related Quality of Life, and Activation Measures

All baseline questionnaires will be sent to patients before the first clinical encounter. If they choose not to participate in the research study, these questionnaires will still aid in clinical decision-making and will be retained in the clinical record. If patients need assistance in completing these questionnaires, it will be offered at the first clinic visit. The questionnaires used are listed below:

A baseline exploratory semistructured questionnaire designed by the team to explore disease impact and behaviorsDisease-specific control questionnaires (Asthma Control Questionnaire [31] and COPD Assessment Test [32]): Baseline measure and then repeated at 3 and 6 months after the first clinical encounterExercise tolerance and symptom measures: Veterans Specific Activity Questionnaire [33], Nijmegen questionnaire [34], and Self Evaluation of Breathing Questionnaire [35] at baseline and repeated at 3 and 6 monthsUse of unscheduled care (including GP visits), steroids or antibiotics for exacerbations, and hospital admissions recorded for each patient at 3 and 6 months compared to their 6 and 12 months visits prior to the MISSION processMeasures of activation and medicine compliance (ASK-12 and Patient Activation Measure [36]) at baseline and 3 and 6 monthsProductivity measures (EuroQoL-5D [37] and Work Productivity and Activity Impairment [38]) at baseline and 6 monthsQuality of life scores: Short Form Health Survey-36 (generic) [39], Asthma Quality of Life Questionnaire (AQLQ) for asthma [40], and St George’s Respiratory Questionnaire for COPD [41]Number of quit-for-life reviews that have resulted in a quit attempt at 3 and 6 monthsPrescription reconciliation at 6 months before and after the clinic visit to assess medication usage

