#### Discontinuation or Withdrawal of Participants from Study Treatment

Participants may withdraw at any point in the study.

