### Data Analysis

#### Description of Analysis Populations

All patients recruited in the study will be included in the analysis population.

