#### Analysis of Quantitative Outcome Data

The objective of all analyses is to examine differences in measured variables between time points.

The following comparisons will be made:

Asthma Control Questionnaire, CAT, and AQLQ: baseline as compared to 3 and 6 monthsEmergency care outcomes: 3 and 6 months prior to study as compared to the 3- and 6-month study periodActivation or medicine compliance (ASK-12 and Patient Activation Measure): baseline as compared to 3 and 6 monthsEuroQoL-5D and weight-bearing physical activity: baseline as compared to 3 and 6 months

All the abovementioned variables are continuous measures. Comparisons between time points will be made using the paired *t* test or the Wilcoxon matched-pairs test, depending on the distribution of the changes in outcome between time points.

Summaries of the measures of monitoring and supported follow-up will be prepared (measures outlined above). Patient satisfaction measures will be summarized descriptively. Numbers and percentages will be used for categorical variables, whereas mean and SD or median and interquartile range will be used for continuous variables. Uncertainty in percentages, means, and medians will be quantified by calculating the appropriate 95% CIs.

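### Excluding patients with missing data and using only paired tests rests each questionnaire comparison on patients with both values, with no check on selective non-response

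*Protocol article*

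**What the plan says.** Three parts of the Data Analysis section bear on this.

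- **Description of Analysis Populations:** "All patients recruited in the study will be included in the analysis population".
- **Analysis of Quantitative Outcome Data:** the Asthma Control Questionnaire (ACQ), COPD Assessment Test (CAT), Asthma Quality of Life Questionnaire (AQLQ), ASK-12, Patient Activation Measure and EuroQoL-5D are each compared between baseline and 3 and 6 months. "Comparisons between time points will be made using the paired *t* test or the Wilcoxon matched-pairs test", the choice depending on the distribution of the changes.
- **Procedure for Dealing With Missing, Unused, and Spurious Data:** "Each outcome will be analyzed using measured data values of all patients", followed at once by "Patients with missing data will be excluded from the analyses". Outlying values lead to a second analysis without them. No second analysis is planned for missing values.

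Elsewhere, the article says of withdrawal that "Participants may withdraw at any point in the study", and of size that "The sample size will be determined by the uptake of appointments and clinic capacity but is projected to be 500 patients and 15 HCPs". The Randomization section says there is none. Unscheduled care is handled differently from the questionnaires: the article has steroid or antibiotic courses and "hospital admissions recorded for each patient at 3 and 6 months", without naming the data source.

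**The concern.** A paired test needs both members of the pair. A patient who returns the baseline and 3-month forms but not the 6-month form contributes nothing to the 6-month comparison, although the 3-month value says something about how that patient was changing. A patient with only a baseline form contributes to no comparison. The result then describes those who kept replying, while the declared population is everyone recruited.

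In a randomised comparison, similar selective loss in both arms would partly cancel. Here the estimate is a within-patient change with no comparator, so nothing offsets it. The complete-case mean change is unbiased for the recruited population only if non-responders changed, on average, as responders did. The plan neither examines that condition nor tests how far the conclusion depends on it.

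The exclusion sentence is also loose. It can be read as dropping a patient from one outcome or from all of them, and the two readings can leave very different numbers.

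**Working it through.** The plan has no figure of its own to reproduce. The 500 is a projection from uptake and clinic capacity, with no stated power, effect size, SD or dropout rate. What follows is illustration under stated assumptions.

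**Inputs.** N = 500 is from Overall Description of Study Participants. The missing share m and the gap g are assumed. Here g is responders' mean change minus non-responders' mean change, in SDs of the change.

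**Bias.** The mean over all recruited is (1 − m)·R + m·NR, where R and NR are the mean changes in responders and non-responders. The complete-case analysis estimates R, so bias = R − [(1 − m)·R + m·NR] = m·(R − NR) = m·g.

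**Precision and error rate.** The number analysed is n = 500·(1 − m). The 95% CI half-width is 1.96/√n. If the true mean change over all recruited patients is zero, the chance that a nominal 5% two-sided test rejects is 1 − Φ(1.96 − m·g·√n) + Φ(−1.96 − m·g·√n). With g = 0.3:

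| m | n | Half-width (SD) | Bias (SD) | Rejection rate |
|---|---|---|---|---|
| 10% | 450 | 0.092 | 0.03 | 10% |
| 20% | 400 | 0.098 | 0.06 | 22% |
| 30% | 350 | 0.105 | 0.09 | 39% |
| 40% | 300 | 0.113 | 0.12 | 55% |
| 50% | 250 | 0.124 | 0.15 | 66% |

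With all 500 the half-width is 1.96/√500 = 0.088 SD, so the loss of precision is modest and the bias is the larger matter. At 20% missing, gaps of 0.2 and 0.5 SD give bias of 0.04 and 0.10 SD and rejection rates of 13% and 52%.

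The table takes all 500 together. A scale used in one disease cohort has a smaller n. The bias m·g is then unchanged, but the rejection rate is lower because the test is less precise.

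**Per outcome or listwise.** With 20% missing on each of four outcomes, per-outcome exclusion leaves 500 × 0.8 = 400 for each. Listwise exclusion with independent missingness leaves 500 × 0.8⁴ = 205. If the same patients tend to miss every form, the listwise number lies between 205 and 400.

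One scale shows that listwise exclusion could not work as scheduled. The list of questionnaires under Patient Assessments collects EuroQoL-5D at baseline and 6 months only, while the analysis section compares it at 3 months as well. On that schedule every patient lacks the 3-month value.

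**The case against.** **The two sections can be reconciled.** A reader might infer a flat contradiction between including everyone recruited and excluding patients with missing data. The sentence just before the exclusion rule speaks of each outcome and of measured values, so the likelier meaning is that everyone is eligible and each outcome uses whoever has data. That stands: the conflict is loose wording. It does not help the paired comparisons, which lose incomplete patients on either reading.

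**Unscheduled care may be unaffected.** A reader might infer that patients who die or leave before 6 months are dropped from the emergency care comparison. The documents do not say so. They do not discuss deaths, do not say whether a shortened follow-up counts as missing, and do not tie these data to questionnaire return. The point for this outcome is only that the handling should be stated.

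**The direction of bias is unknown.** A reader might infer bias towards benefit, because the article says "Such patients often struggle to engage with the structured, proactive care approach to chronic disease management advocated for asthma and COPD". That describes the target group before the service, not who returns forms. Participants have already attended a clinic and consented, which selects for engagement. Patients who feel better may also stop replying. The documents support no direction.

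**A mixed model is not a cure.** It assumes missing at random, so it does not by itself remove bias from loss that depends on the unseen values. This is correct, and is why the sensitivity analysis belongs with it.

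**Context.** This accompanies a quality-improvement project with an uncontrolled design, which has larger limitations. That is fair, but the rule is written down, so it is not detail left to an analysis plan, and improving it costs little.

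**Conclusion.** The point holds for the questionnaire outcomes. As written, each comparison uses only patients with both values, discards partial follow-up, and has no responder comparison or sensitivity analysis for missing data. In an uncontrolled before-and-after design, selective non-response goes straight into the estimated change.

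The size is m·g: 0.03 to 0.15 SD for 10% to 50% missing and a 0.3 SD gap. Both inputs are assumptions, so this shows what could happen and is not an estimate for this study. At the low end the effect is small. The ambiguity between per-outcome and listwise exclusion is a separate wording fault that one sentence removes. For unscheduled care no error is shown, only a rule worth stating. This is a cheap improvement, not a defect that invalidates the study.

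**What to change.** 1. State that exclusion is per outcome and not listwise, and that the declared population means everyone recruited is eligible for every outcome relevant to their condition.
2. Analyse each questionnaire with a repeated-measures mixed model, taking baseline, 3- and 6-month values as responses, as scheduled for that scale. Include every patient with at least one value. Use baseline covariates already collected, such as age, smoking status and prior unscheduled care, and let them interact with time so that they can inform the change. Include cohort only where a scale spans cohorts; it has no place for a single-disease scale such as the AQLQ.
3. Report the numbers and baseline characteristics of patients with and without follow-up at each time point.
4. Add a delta-based sensitivity analysis that shifts non-responders' change by a range of values and shows where the conclusion alters.
5. For unscheduled care, state that events are counted for every consented patient whether or not questionnaires are returned. Where follow-up is cut short by death or withdrawal, use a count model with log observed time as an offset. Report deaths.

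**Cost.** Revised wording and modest programming. No new questionnaire data are needed, which matters because the article's Results section reports enrolment complete and analysis underway. Whether event dates up to death or withdrawal are held has to be confirmed, since the data source is not stated. The price is a missing-at-random assumption in the main model, which step 4 probes.

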#### Interim Analysis and Criteria for Early Study Termination

No interim analyses are planned. A single analysis will be performed when all patients have completed the study. The study will not be terminated early based on any study data.

### Patient Public Involvement

#### Study Design

The MISSION ABC clinic has been formed by feedback from patients’ involvement in the prior pilots (MISSION Asthma and MISSION COPD). All relevant outcomes of patients will be recorded. All paperwork, such as Participant Information Sheets and educational literature, is reviewed by our patient participants before distribution.

#### Study Implementation

The steering group for MISSION ABC includes the chair of a local Patient Action Group and patients from the MISSION COPD pilot project and local Breathe Easy Groups. Ongoing data such as those generated from the cyclical evaluation of clinics will be reviewed, and the group will contribute to informing and delivering change.

#### Dissemination

Lay summaries of the results of the research will be written together with the Patient and Public Involvement members, disseminated both in verbal and written formats to local groups such as Breathe Easy groups, and written in appropriate formats for the Trust social media accounts. The Patient and Public Involvement members will be invited to present data locally and nationally, where appropriate.

## Results

The project was funded in 2017 and enrollment was completed in 2018. Data analysis is currently underway, and the first results are expected to be submitted for publication in April 2019.

## Discussion

This is a unique participatory action research study using both qualitative and qualitative methodology involving patients, carers, and HCPs. The longer-term impact of the service will be evaluated using clinical and health service outcomes that will inform decisions on future service implementation.

## Abbreviations

ASK-12: Adherence Starts with Knowledge questionnaire-12
AQLQ: Asthma Quality of Life Questionnaire
COPD: chronic obstructive pulmonary disease
FeNO: fractional exhaled nitric oxide
GP: general practitioner
GOLD: Global Obstructive Lung Disease
GRASP: Guidance on Risk Assessment in Stroke Prevention
HCP: health care professional
MISSION ABC: Modern Innovative Solution Improving Outcomes in Asthma, Breathlessness, and COPD
NICE: National Institute for Health and Care Excellence
